#### Date collection

Prior to intervention roll-out, baseline data will be retrospectively collected for the prior 12 months at each of the selected study sites, including the number of women accessing care for HIV care and treatment services each month; the number of women screened for cervical cancer through standard of care protocols; the proportion of screen-positive women who then received treatment or referral for treatment, and the length of time between screening positive and receiving treatment, if appropriate. Data will be collected by study team members (physician, nurse, or medical technicians) utilizing a paper-based instrument and then uploaded into a password-protected, tablet-based, online research data capture (REDCap) database. This method allows for the recording of demographic information, medical and medication history, and any pertinent laboratory test results. Data quality control will be conducted by study investigators who will review all completed paper-based study instruments and confirm the accuracy of data entered into REDCap.

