Mozambique has one of the highest burdens of cervical cancer in the world, with an age-standardized incidence rate of 50.2 and mortality rate of 38.7 per 100,000 women [12, 13]. Cervical cancer ranks as the most frequent cancer among women in Mozambique, with an estimated 5,300 new cases and 3,800 related deaths reported each year [14]. The prevalence of HIV in women ages 15–49 in Mozambique was estimated at 15.4% in 2021 [15]. Cervical cancer screening was introduced in the country in 2009 using VIA followed by immediate treatment with ablation (cryotherapy or thermal ablation) or referral for LEEP if the cervical lesion(s) did not meet the criteria for ablation [13, 14, 16]. One challenge is that many of the women who screen positive with VIA, are not undergoing treatment with ablation at the same visit. As a result, many women who screen positive are subsequently lost to follow-up and never receive treatment. Most women with cervical cancer in Mozambique therefore present with advanced stage disease and the majority die of their disease.

The current WHO recommendation for cervical cancer screening utilizing primary HPV testing is now being endorsed by the Mozambican Ministry of Health (MOH) [17]. Initial studies showing the feasibility of this approach in the Mozambican context have been encouraging, with women participants reporting a preference for self-sampling approaches [18]. However, these studies to date were conducted amongst eligible women accessing family planning services in higher-resource areas near the nation´s capital of Maputo. Studies designed to evaluate best practices for implementation among a high-risk, lower-resourced population within Mozambique´s already busy HIV care and treatment services are needed to provide the evidence-base required to take this approach to scale.

We summarize below our protocol for a hybrid type III effectiveness-implementation study of HPV self-collection within the HIV care and treatment program in Chókwè District, Mozambique, describing the conceptual frameworks that have guided its development, the different phases that will be employed throughout its implementation, and the measures we propose for evaluating its implementation and effectiveness.

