### Aims/objectives

The overall aim of this study is to evaluate implementation best practices for deploying a *Screen-Triage-Treat* approach to cervical cancer screening utilizing self-collected HPV DNA testing among HIV-infected women in care within select health facilities in Chókwè District, Mozambique. The main objectives of this study are:To develop an in-depth understanding of the HPV *Screen-Triage-Treat* care cascade within the HIV care and treatment services based on a collaborative, exploration-focused process with local stakeholders.To evaluate the effectiveness of the *Screen-Triage-Treat* approach to cervical cancer screening utilizing self-collected HPV DNA testing.To use the Consolidated Framework for Implementation Research (CFIR) to identify factors that explain site-level and provider-level variation in the implementation of the *Screen-Triage-Treat* approach to cervical cancer screening utilizing self-collected HPV DNA testing.

Table 1 shows the SPIRIT diagram including the schedule of enrollment, intervention, and assessment.

**Table 1 Tab1:** SPIRIT diagram: schedule of enrollment, intervention, and assessment

Study Period	Pre-Implementation Phase	Implementation Phase	Follow-up Phase	Post-implementation Evaluation
Timepoint	Month −2 to 0	Month 0–30	Month 1–30	Month 31–33
Enrollment:				
Site preparation and staff training	X			
Two-week pilot assessment period	X			
Model participant enrollment (1–2/day)		X		
Participant eligibility screening		X		
Informed Consent		X		
Intervention:				
Self-collected HPV DNA testing (Screen)		X		
HPV result reporting (same-day CHC; weekly in periphery)		X		
VIA and thermal ablation if eligible (Triage-and-treat)		X		
Referral to higher level of care for LEEP/colposcopy in not eligible for ablation		X		
Assessments:				
Baseline retrospective data (past 12 months)	X			
Process mapping/group model building workshop and qualitative interviews (Objective 1a-c)	X	X		
Quantitative data collection (HPV, VIA, treatment rates)		X		
Implementation Outcomes (adoption, fidelity, reach, acceptability)		X	X	
Qualitative provider interviews (CFIR domain)			X	
Statistical analysis of primary outcome (proportion of HPV + women treated, Objective 2)			X	
Analysis of secondary outcomes (implementation outcomes, Objective 3)			X	
Dissemination workshops and final reporting				X

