#### Outcome measures

Our primary outcome measure is the number of women screened and the proportion of screen-positive women successfully undergoing treatment. Secondary outcomes measures will include other implementation outcomes (see Specific Objective 3 below), and if successful, will be utilized to inform future research to take this approach to scale across Mozambique.

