#### Sample size and power calculations

We used our primary outcome, more specifically, the proportion of HPV screen positive women that will successfully undergo treatment, to power the study. We used preliminary data to estimate a sample size sufficient to detect, with 90% power, an improvement of at least 15% in the proportion of women undergoing treatment compared to the current standard of practice. CHC currently sees approximately 1,200 HIV adult outpatient visits per month, of which 52% are female (*n* = 624) and approximately 75% of women are between the ages of 25–49 years (*n* = 468). Of these, we conservatively expect approximately 60% will not have been screened in the last three years and meet screening eligibility (*n* = 280). Based on preliminary data, the prevalence of HPV-positivity among WLWH was estimated to be approximately 40%; however, in our calculations, we again took a more conservative approach and assumed an HPV prevalence of 35% (*n* = 98). Under the current standard of care scenario we estimate that approximately 36% of HPV screen positive women go on to receive treatment (CHC currently performs, on average, 35 thermal ablation procedures per month). Figure 4 below shows statistical power curves to detect improvements, through utilization of the HPV self-testing *Screen-Triage-Treat* approach, varying from 10 to 20% in the proportion of HPV-screen positive women undergoing same day thermal ablation, compared to standard of care. We used a type-I error fixed at 5%, two-sample, two-sided binomial test, and assumed trimestral cumulative data to plot the curves, for different prevalences of HPV. Calculations were performed using the R software (*pwr* R package) [28]. Based on Fig. 4, we will be able to detect over 15% improvements in the proportion of HPV-screen positive women undergoing same day thermal ablation compared to standard of care, while assuming a prevalence of 35% or even lower at 25%, with at least 90% power.

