#### Statistical analysis plan

Using data captured during implementation of the *Screen-Triage-Treat* approach for cervical cancer screening, we will evaluate intervention fidelity as a function of 1) *Completion Rate*: the proportion of enrolled women who turned in a self-collected sample for HPV DNA testing; 2) *Test Result Notification Rate*: the proportion of women who were notified of their HPV DNA test result on the same day as sample collection; and 3) *Treatment Rate*: the proportion of screen-positive women who were treated with thermal ablation, if appropriate, or referral for higher level of care.

Patients’ characteristics and clinical values will be summarized in tables and figures. Continuous variables will be presented as medians and interquartile ranges. Categorical variables as frequencies and percentages. Descriptive statistics will be done for the overall population and stratified intervention status and study site. Continuous variables will be compared via the Mann–Whitney-Wilcoxon test, and categorical variables will be compared via the chi-square test. We will use a generalized linear model (GLM) with the logit link to and perform an interrupted time series to assess the impact of the intervention and the proportion of patients who subsequently underwent treatment for cervical cancer. The model will regress the outcome on intervention status (binary variables, yes/no), calendar time (in months), and an interaction between the two terms. By doing this we will be able to assess the immediate impact of the intervention (also known as level change) as well as its effect over time (sustained effect of the intervention) compared to the counterfactual scenario of no intervention being implemented. Analysis and comparisons will be performed overall, combining all sites, as well as being stratified by health facilities. We will adjust for relevant demographic and clinical characteristics, such as age, CD4 count, and viral load, among other factors. Continuous variables will be modeled via restricted cubic splines. We will again use GLM with a gaussian link to estimate the impact of the intervention on the number of WLWH diagnosed with HPV, adjusting for the same covariates as above, and following the same steps as above (e.g., another interrupted time series). If the normality assumption is violated, we plan to use ordinal regression models as an alternative. We do not expect issues with statistical over-fitting.

### Specific objective 3

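### Reading baseline treatment status before roll-out, with no screen-to-treatment window, can create a spurious level change in favour of the intervention; its size depends on an undocumented treatment delay

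*Protocol article*

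**What the plan says.** The Date collection section under Specific objective 2 fixes the timing: "Prior to intervention roll-out, baseline data will be retrospectively collected for the prior 12 months at each of the selected study sites". Table 1 marks this extraction only in the pre-implementation column (month −2 to 0) and schedules no later update. The items collected include "the proportion of screen-positive women who then received treatment or referral for treatment, and the length of time between screening positive and receiving treatment".

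The plan words the outcome in several ways:
- Outcome measures: "the proportion of screen-positive women successfully undergoing treatment", with no time limit.
- Sample size and power calculations: "proportion of HPV-screen positive women undergoing same day thermal ablation".
- Date collection, and the Treatment Rate in the Statistical analysis plan: referral counts alongside treatment.

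The Statistical analysis plan fits a logit model with intervention status, calendar month and their interaction. One stated purpose is to "assess the immediate impact of the intervention (also known as level change"; the other is to estimate the effect over time against a no-intervention counterfactual.

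**The concern.** The Background reports that "many of the women who screen positive with VIA, are not undergoing treatment with ablation at the same visit", and the baseline form records the delay to treatment, so some late treatment under standard of care is to be expected.

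A woman who screened positive eleven months before extraction has had eleven months to be recorded as treated. One who screened positive in the final baseline month has had less than one. Anyone treated after extraction stays recorded as untreated. In the intervention period most women have much longer to be counted, because follow-up in Table 1 runs to month 30.

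If delays are material, the recorded baseline proportion drifts down towards roll-out for a reason unrelated to care. The model extrapolates that level and slope as its counterfactual. Both the immediate and the sustained effect are then biased towards the intervention.

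**Working it through.** **Plan's own figures.** 280 × 0.35 = 98 positives a month. 35 / 98 = 35.7%, the plan's approximate 36% treated. The target is a 15-point gain, from 36% to 51%.

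**Inputs from the plan.** 36% treated, 98 positives a month, 12 baseline and 30 intervention months, and the stated logit model.

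**Assumptions not in the plan.**
- The intervention has no effect: 36% are eventually treated in both periods.
- A share *s* of treated women are treated at the screening visit. The rest follow an exponential delay with median *m* months, so λ = ln 2 / *m*.
- Women are indexed by month of positive screen, evenly within the month, with 98 positives a month in both periods.
- Baseline status is read at roll-out. Intervention status is read at month 33, the end of Table 1.

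**Formula.** With follow-up *f*, the expected recorded proportion is 0.36 × [*s* + (1 − *s*)(1 − e^(−λf))]. In the last baseline month *f* runs from 0 to 1, and the bracketed delay term averages 1 − (1 − e^(−λ))/λ.

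**Example, *s* = 0.5, *m* = 2.** λ = 0.3466 and (1 − 0.7071)/0.3466 = 0.845. The last baseline month therefore reads 0.36 × (0.5 + 0.5 × 0.155) = 20.8%. The first, with 11 to 12 months of follow-up, reads 35.7%.

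**Model fitted to the expected proportions, no true effect:**

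| Same-visit share | Median delay (months) | Last baseline month | Fitted level before → after | Change (points) | OR | z |
|---|---|---|---|---|---|---|
| 100% | none | 36.0% | 36.0% → 36.0% | 0 | 1.00 | 0 |
| 50% | 0.23 (one week) | 30.3% | 34.1% → 36.0% | +1.9 | 1.09 | 0.6 |
| 75% | 0.5 | 31.1% | 34.1% → 36.0% | +1.9 | 1.09 | 0.6 |
| 50% | 1 | 23.0% | 29.1% → 36.2% | +7.1 | 1.39 | 2.2 |
| 50% | 2 | 20.8% | 25.0% → 36.9% | +11.9 | 1.75 | 3.7 |
| 25% | 3 | 11.9% | 16.6% → 38.3% | +21.7 | 3.11 | 6.9 |

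In the 50%, 2-month row the gap from the extrapolated counterfactual grows to about 20.9 points at month 12.

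**Sensitivity to baseline numbers.** 98 is the projected HPV-positive yield; the number of baseline positives under standard of care is not given. With 35 a month before roll-out (illustrative) and 98 after, the point estimates barely move. z falls from 3.7 to 2.4 (median 2 months) and from 2.2 to 1.45 (median 1 month).

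**Sensitivity to closing date.** If intervention status is read at month 30 and half of treated women are delayed, a mean delay of 1 month gives OR 1.32 (30.9% → 37.1%). A mean of 2 months gives OR 1.64 (27.2% → 38.0%).

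**Check of the remedy.** A 3-month window (illustrative) is applied to both periods and baseline is read after it has closed. Both levels are then 0.36 × (0.5 + 0.5 × 0.875) = 33.75% for *m* = 1 and 29.6% for *m* = 2, with OR 1.00. Reading baseline two months late without a window only shrinks the artefact, to +1.9 and +6.5 points.

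**The case against.** A reader might infer that the series must show a false effect, or that it could be as large as 22 points. The documents do not support either statement, for these reasons:

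- **Same-visit or never.** The Background goes on to say that many women not treated at once are lost and never treated. Women who are never treated cause no truncation; only delay among the roughly 36% who are treated matters. The documents do not say how common that is.
- **Same-day ablation.** If that is the outcome, as the power section words it, truncation cannot occur. But Outcome measures sets no such limit. At the three peripheral sites results come back the following week, so treatment on the day of sample collection cannot follow from the HPV result there.
- **Referral.** If referral counts and is entered at the visit, fewer women are exposed and the artefact shrinks. The table does not model this.
- **Indexing.** The 36% comes from monthly procedure counts over expected positives. Treatments counted by month of procedure would not be truncated. The baseline item reads more naturally as following screen-positive women forward, but the plan does not say which applies.
- **Analyst's remedy.** Time to treatment is collected, so a fixed window could be applied and incomplete baseline months dropped. This would work. With a 3-month window it leaves 12 − 3 = 9 baseline months.

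The full protocol or analysis plan may set a window. What stands is that this article fixes an extraction date that, with an unlimited outcome, puts any under-count at the break.

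**Conclusion.** The mechanism and its direction hold: with the stated extraction timing and no window, any delayed standard-of-care treatment is under-counted in the last baseline months, and the level change is biased in favour of the intervention.

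The size is conditional. It is nil without delayed treatment or with a same-day outcome. It is about 2 points when half of treated women wait a median of one week. It is roughly 7 to 12 points when half wait a median of 1 to 2 months. The last range is large against the 15-point target, but it rests on an assumed exponential delay, indexing by screen month and no credit for referral. Statistical significance is weaker if baseline positives number fewer than 98 a month. The 22-point figure needs three quarters of treated women delayed with a 3-month median, which nothing in the documents establishes. The plan's power figures do not depend on this point.

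**What to change.** 1. State one outcome definition and use it in Date collection, Outcome measures, the power section and the analysis plan, saying whether referral counts.
2. Measure it within the same fixed number of days after the positive screen in both periods. This is a counting rule only and does not affect when any woman is treated.
3. Assign each woman to the month of her positive screen. Treatments after roll-out of women screened at baseline stay with their baseline month.
4. Read baseline status, or re-read it from the same registers, only after the window has closed for the last baseline woman. Otherwise, end the 12-month baseline one full window before extraction. Apply the same closing rule to the last intervention cohorts.

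The cost is a revised outcome sentence plus one register re-check after roll-out, or a slightly earlier baseline year. Treatments later than the window go uncounted, equally in both periods.

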### Study setting

This study will take place at Carmelo Hospital of Chókwè (CHC), as well as three peripheral health facilities (*Centro de Saúde (CS) da Cidade; CS Urbano; and CS de Chalucuane*) within the district network of facilities that respond to CHC. CHC is a reference hospital for HIV and TB in the district of Chókwè, a large district in Gaza Province in southern Mozambique (Fig. 1). Chókwè District is predominantly rural, with a surrounding catchment population of approximately 200,000 inhabitants. Agriculture is the predominant source of local income for roughly 60% of the population, while approximately 40% of the population migrates seasonally to South Africa, seeking work in the mines, a recognized driver of the district’s high HIV and TB burden [20]. Per the latest national HIV prevalence study in 2021, Gaza Province had the highest provincial HIV prevalence in the country at 20.9% [15].

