#### Study participants and enrollment period

Women accessing health care for HIV care and treatment services at CHC, between the ages of 25–49 years of age will be approached for enrollment into the study and subsequent cervical cancer screening. Following the “Model” Participant period, enrollment of participants will continue for a total of 30 months (Table 2).

**Table 2 Tab2:** Inclusion and Exclusion criteria

Inclusion Criteria	Exclusion Criteria
Women 25–49 years, accessing HIV care and treatment services	Physical or mental impairment that inhibits participation in the study
Not being pregnant	Pregnant women or < 6 weeks post-partum
Patients with a cervix (women who have undergone a total hysterectomy with removal of the cervix are not eligible)	

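### The interrupted time series extrapolates from 12 baseline months with no seasonal term; 24 months of baseline counts and one seasonal term would cheaply strengthen it

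*Protocol article*

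**What the plan says.** Under Specific objective 2, the Date collection section states that "baseline data will be retrospectively collected for the prior 12 months at each of the selected study sites". The enrolment section states that "enrollment of participants will continue for a total of 30 months". The Statistical analysis plan gives the time-series terms: "The model will regress the outcome on intervention status (binary variables, yes/no), calendar time (in months), and an interaction between the two terms". From these it reads a level change and "its effect over time (sustained effect of the intervention) compared to the counterfactual scenario of no intervention being implemented". The same steps are repeated for a second series, the number of women diagnosed with HPV.

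On adjustment, the plan says: "We will adjust for relevant demographic and clinical characteristics, such as age, CD4 count, and viral load, among other factors". It adds: "Continuous variables will be modeled via restricted cubic splines". Neither sentence names season or month of year, and the Limitations section does not mention season. The Study setting section says that "approximately 40% of the population migrates seasonally to South Africa, seeking work in the mines".

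**The concern.** The counterfactual for up to 30 months of follow-up is a line fitted to 12 monthly points, one for each calendar month. A full year of baseline may seem to balance season out. It balances the mean but not the slope: a straight line through one annual cycle tilts up or down according to where in the cycle it starts. The model treats that tilt as the secular trend and carries it forward. If the outcome is seasonal, part of the level change and more of the sustained effect could then be artefact, and the artefact could as easily hide a real benefit as create a false one.

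A second weakness does not depend on season. Twelve points fix a slope poorly, and the error grows with the distance extrapolated. The sustained effect is one of the two quantities that the plan promises from this model.

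**Working it through.** **The plan's own figures.** 98 HPV-positive women per month × 30 = 2,940, and 15% of that is 441, as stated. For 36% against 51%, two-sided 5%, with 3 × 98 = 294 women per quarter on each side, power is 95.8%, which agrees with the stated 90% or more. At 25% prevalence (210 per quarter) it is 87.6% for exactly 15 points and 91.3% for 16; the text says over 15%. These figures concern a two-sample comparison and do not describe the time-series model.

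**Inputs.** From the document: 12 pre-launch months (t = 1 to 12), 30 post-launch months (t = 13 to 42), and the terms 1, t, D and D×t. Assumed: a yearly sine wave of amplitude A, the same before and after launch; no intervention effect; linear scale. A = 2, 3 and 5 points are illustrations, because the document gives no amplitude.

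**False slope from one cycle.** The fitted baseline slope is Σ(t − 6.5)y / Σ(t − 6.5)², with denominator 143. Over all timings of the cycle, the largest numerator is A × 6/sin(π/12) = 23.18A. The largest false slope is therefore 23.18A/143 = 0.162A per month, or 0.486 points per month at A = 3.

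**Carried forward, A = 3.** The last month is 42 − 6.5 = 35.5 months from the baseline centre, so the counterfactual is wrong by up to 35.5 × 0.486 = 17.3 points. The post-launch line, which covers two and a half cycles, adds about 0.4, giving 17.7. At the first post-launch month, 6.5 × 0.486 = 3.2, and the same addition gives 3.5. The bias scales with A:

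| Assumed swing | Largest false level change | Largest false month-30 effect | Average absolute month-30 effect over launch time |
|---|---|---|---|
| ±2 points | 2.4 | 11.8 | 7.5 |
| ±3 points | 3.5 | 17.7 | 11.2 |
| ±5 points | 5.9 | 29.4 | 18.6 |

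The sign depends on launch timing. With 24 baseline months and still no seasonal term, the largest month-30 figure at ±5 falls from about 29 to 9.

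**Logit version.** A binomial-logit fit with 98 positives per month (simulated, no true effect) gave false-positive rates, averaged over launch month, of 7% (level) and 8% (slope) at ±2 points, and 22% and 30% at ±5. With only 30 baseline positives per month, the ±5 rates are 10% and 12%. With one sine/cosine pair and 98 per month, they return to 4.7–5.6% (level) and 5.3–5.7% (slope).

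**Count of HPV diagnoses.** A 10% swing on 98 per month (assumed) has amplitude 9.8. By the same scaling, the false level change is up to 3.55/3 × 9.8 = 11.6 per month and the false month-30 effect up to 17.65/3 × 9.8 = 58 per month.

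**Precision without season.** The month-30 effect is the post-launch line at t = 42 minus the extrapolated baseline line. In units of one monthly point's variance:
- Post-launch line: 1/30 + 14.5²/2,247.5 = 0.127.
- Baseline line, 12 months: 1/12 + 35.5²/143 = 8.896. The sum is 9.023, so the SE multiplier is 3.00.
- Baseline line, 24 months: 1/24 + 41.5²/1,150 = 1.539. The sum is 1.666, so the multiplier is 1.29.

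With 98 screen-positive women per month, which is an assumption for the baseline, the monthly SE is √(0.36 × 0.64/98) = 4.85 points. The month-30 SE is then about 14.5 points with 12 baseline months and 6.3 with 24.

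**Limit of the seasonal term.** If a ±3-point season existed only before launch, a shared sine/cosine pair with 12 baseline months would still leave up to about 15 points of false effect at month 30 and 7 at month 12.

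**The case against.** The strongest reply is that no seasonal signal in the outcome is documented. The 40% describes the general population seeking mine work, not women aged 25–49 in HIV care. The main modelled outcome is a proportion among screen-positive women, so lower attendance can shrink the denominator without moving the proportion. This stands: the bias is conditional, and at ±2 points the excess false-positive rate is small. The count of HPV diagnoses depends on attendance directly and is more exposed.

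The larger figures are worst cases over launch time, at a month-30 contrast that the plan does not name. This also stands, which is why the averages are given. The false level change stays well below the 15-point target at every amplitude shown.

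A reader might infer that 12 baseline months make season and trend inseparable. They do not: under a season shared across both periods, the 30 post-launch months identify it, and adding the sine/cosine pair takes the bias to zero in the linear calculation. Nor is that zero guaranteed, since the intervention changes how and when results reach women and so may change the seasonal pattern.

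The 98 women per month is the expected yield of HPV testing. Baseline screening used visual inspection, and its screen-positive counts are not given, so the SEs in points are illustrative. The multipliers 3.00 and 1.29 need only equally precise monthly points.

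Finally, this is a condensed article, and a full analysis plan could add season under its open list of adjusters. That is possible for the model term. But the baseline window is a data-collection decision stated here, and an analysis plan alone cannot lengthen it. The general caveats on confounding under Limitations do not address it either.

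**Conclusion.** The point holds as a cheap improvement. The stated model has no seasonal term and extrapolates up to 30 months from 12, so a yearly swing of a few points would bias the level change modestly and the late sustained effect substantially, in either direction. That part is conditional on season affecting the outcome, and the amplitudes are assumed. The precision part is not conditional on season: relative to one monthly point, the month-30 SE more than halves (3.00 to 1.29) when the baseline goes from 12 to 24 months.

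A reader might go further and conclude that season will produce a false sustained effect, or that the study cannot meet this part of Objective 2. The document does not support either. It reports no seasonal variation in treatment or diagnosis, names no month-30 estimand, and bases its power on a different comparison.

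**What to change.** In Date collection, and in the matching baseline row of Table 1, extend the retrospective abstraction of the same monthly counts from 12 to 24 months where the registers allow. In the Statistical analysis plan, add one sine/cosine pair with a 12-month period (or month of year) to both time series, and state that it removes seasonal bias only if the pattern is the same before and after launch.

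If only 12 baseline months can be had, keep the seasonal term, treat the level change as the main time-series result, and report the sustained effect as exploratory with its interval, without relying on the late extrapolation.

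The cost is two extra parameters, which raise the SE of the level change by about 8–9% with 12 baseline months and 2–3% with 24, plus abstraction of 12 more months of existing counts at four facilities. The abstraction is retrospective, so participants bear no added burden. Whether the registers hold 24 comparable months has to be checked first.
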